### Sample size

The calculation of sample size will be based on the change of PSQI scores. A systematic review indicated [37] that in an acupuncture group and a sham acupuncture group, a clinically significant therapeutic effect is defined as a PSQI score gap of at least 2.7 points, and we estimate that there will be 3 points in each gap between the two groups after treatment. Factors such as contamination, noncompliance, and dropout will be considered; the dropout is determined to be 15%. Therefore, each group will need approximately 30 participants to obtain statistically significant results, and we will recruit 60 participants.

### Randomization and allocation concealment

Eligible participants will be randomly assigned to the two groups in a 1:1 ratio. SPSS 22.0 software (IBM, Armonk, NY, USA) will be used to generate a random number table, which will be executed by people who have no direct contact with the participants or assessor. The random numbers will be sealed in random opaque envelopes to ensure the confidentiality of distribution.

### Blinding

Grouping results will be kept secret from participants, evaluators, and statisticians. The two groups of patients will be similar in point positions and acupuncture operation, and the patients will wear eyeshades during acupuncture to optimize the participants’ blindness. All participants will be asked to indicate whether they have received acupuncture or sham acupuncture within 5 min after treatment to assess blindness. The grouping results will not be kept secret from the acupuncturists who will provide the interventions, as they will carry out the treatment.

### Informed consent

As stated in the Declaration of Helsinki, we will inform participants about the details of our research, including objectives, characteristics, potential benefits and risks, other available treatment options, and the rights and obligations of the participants. After obtaining written informed consent, participants will be enrolled in the study. During the trial, if new ideas on research ethics emerge, the informed consent will be revised and resubmitted to the ethics committee. After approval, the informed consent will be required again. If a participant exits the trial, related data will be retained for final analysis.

### Safety monitoring

After recruitment and before randomization, all participants will undergo routine blood and liver and kidney function tests to identify and exclude patients with severe heart, liver, or kidney diseases. At the end of the study, participants will be re-examined to assess any possible side effects of the intervention. The scholars will properly address, analyze, and document adverse events (AEs) that may result from acupuncture, such as syncope, local infection, and subcutaneous hematoma. Any serious AEs associated with the trial will be immediately reported to the main researchers. The researchers will also record all other unexpected reactions as AEs, even if they are not necessarily associated with the acupuncture intervention.

### Data collection and management

The designed case report form (CRF) will collect each participant’s data and transfer them into a database based on the observed indicators. It will be kept in the archives of Jiangsu Hospital of Traditional Chinese Medicine for more than 10 years. Only members of research team will have access to the data.

### Statistical analysis

In this study, SPSS 22.0 software (IBM, Armonk, NY, USA) will be used to analyze the data. The measured data will be expressed as mean ± standard deviation, and the count data will be expressed by the ratio or composition ratio. For comparing measured data between the two groups, first normal analysis will be performed. A *t*-test will be used for the measured data conforming to normal and homogeneity of variance, and a non-parametric rank sum test will be used for non-normally distributed measured data. The data will be counted by the chi-square test or Fisher’s exact test. *P* values ≤ 0.05 will be considered statistically significant.

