**Methods/design:**

A single-center, single-blind, randomized, placebo-controlled trial will be conducted at Jiangsu Hospital of Traditional Chinese Medicine. A total of 60 patients will be registered. Eligible participants will be randomly divided into acupuncture group and sham acupuncture group (*n* = 30 cases in each group). Patients in both groups will be treated once every other day, three times per week for 4 weeks. The primary outcome measures are Pittsburgh Sleep Quality Index (PSQI) and concentrations of adrenocorticotropic hormone (ATCH), corticotrophin-releasing hormone (CRH), and cortisol (CORT). Secondary outcome measures are Insomnia Severity Index (ISI) and Fatigue Severity Scale (FSS).

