### Outcome measures

#### Primary outcome measures

PSQI is a questionnaire for assessment of individuals’ sleep quality comprising seven parts, such as sleep quality, time to fall asleep, sleep time, sleep efficiency, sleep disorders, the taking of sleeping pills, and daytime dysfunction. The total score of PSQI is 0–21 and is inversely proportional to sleep quality; the higher the PSQI score is, the worse the sleep quality is. PSQI > 5 can be a reference threshold to judge sleep quality. In the present study, PSQI > 5 will be taken as the inclusion criterion for chronic insomnia. PSQI will be evaluated before treatment and after 4 and 8 weeks of treatment.

For determining concentrations of ACTH, CRH, and CORT, 4 ml of venous blood will be drawn and anticoagulant will be added. Plasma will be separated by centrifugation at 3000 rpm and then stored in a refrigerator (− 70 °C). A Beckman automatic chemiluminescence enzyme free analyzer (Beckman Coulter, Inc., Brea, CA, USA) will be used for the determination. Two venous blood samples from each participant will be taken at 8 am on the day before the treatment and 8 am on the day after the end of the final treatment.

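### Continuous outcomes, including all four primary measures, are compared without baseline adjustment although baseline values are collected; this costs precision but causes no bias

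*Protocol article*

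**What the plan says.** The Statistical analysis section of the protocol article fixes one route for continuous data. It opens with a check of the distribution: "For comparing measured data between the two groups, first normal analysis will be performed". Where that check is passed and variances are equal, a two-group t-test applies. Where normality fails, the plan turns to ranks: "a non-parametric rank sum test will be used for non-normally distributed measured data". On the threshold, it says that P "values ≤ 0.05 will be considered statistically significant". No covariate and no longitudinal model is named.

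The primary outcomes are PSQI, ACTH, CRH and CORT (Abstract); ISI and FSS are secondary. Table 1 schedules all six at baseline. The three questionnaires are repeated post-treatment and at follow-up, and the hormones post-treatment only. For PSQI the outcome section confirms: "PSQI will be evaluated before treatment and after 4 and 8 weeks of treatment".

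The section does not define the quantity tested. Elsewhere the article speaks of change: the Objectives compare hormone changes from before to after treatment, and the Sample size section rests on the change in PSQI.

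On attrition, the Sample size section says "the dropout is determined to be 15"%, and the Informed consent section says "If a participant exits the trial, related data will be retained for final analysis".

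**The concern.** A baseline value of an outcome usually predicts its later value. A two-group test of post-treatment values ignores that information. A test of changes uses it, but with a fixed weight of one rather than the weight the data support.

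In a 60-patient trial, chance differences between arms at baseline can be appreciable. With equal SDs at both visits and correlation r, a chance baseline difference D shifts a post-score comparison by r × D and a change-score comparison by (r − 1) × D, that is, in the opposite direction. ANCOVA removes both shifts. At stake are the width of the confidence interval and the power for all four primary comparisons. This is a method the article states, not a detail it leaves open, so an analysis plan that adjusted for baseline would replace the stated method.

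**Working it through.** **Inputs from the article.** Difference 3 PSQI points; dropout 15%; 30 per arm, so 30 × 0.85 = 25.5 completers per arm; significance level 0.05.

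**Assumptions.** Two-sided testing; equal SDs at baseline and post-treatment; baseline/post-treatment correlation r of 0.3, 0.5 or 0.7; SD of 3.25, 3.75 or 4.5. The article states none of these, nor the power.

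**Step 1: the plan's own figure.** The 30 per arm can be neither confirmed nor refuted without an SD and a power. Solving backwards with n = 2 × (1.96 + z)² × SD² / 3², rounding up, then dividing by 0.85 and rounding up:

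- 80% power (z = 0.84): 30 per arm follows for SD 3.71 to 3.78. At SD 3.75, n = 24.5, so 25, and 25 / 0.85 = 29.4, so 30.
- 90% power (z = 1.28): 30 per arm follows for SD 3.21 to 3.27.

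SD 3.25 and 3.75 therefore represent the two usual designs, and 4.5 is a less favourable case.

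**Step 2: standard errors.** Relative to a test of post-treatment scores, the variance is 1 − r² for ANCOVA and 2(1 − r) for change scores. ANCOVA relative to change scores is therefore (1 − r²) / [2(1 − r)] = (1 + r)/2. The SE ratio is the square root.

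| r | SE ratio, ANCOVA / post score | SE reduction | SE ratio, ANCOVA / change score | SE reduction |
|---|---|---|---|---|
| 0.3 | √0.91 = 0.954 | 5% | √0.65 = 0.806 | 19% |
| 0.5 | √0.75 = 0.866 | 13% | √0.75 = 0.866 | 13% |
| 0.7 | √0.51 = 0.714 | 29% | √0.85 = 0.922 | 8% |

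Both variance factors are below 1 for every r between 0 and 1, so the direction does not depend on which quantity is tested.

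**Step 3: power** (noncentral t, difference 3, 25.5 per arm). At r = 0.5 the variance factor is 0.75 on both readings, so one row serves both:

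| SD of the quantity tested | Unadjusted | ANCOVA, r = 0.5 |
|---|---|---|
| 3.25 | 90% | 96% |
| 3.75 | 80% | 90% |
| 4.5 | 65% | 77% |

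At r = 0.5, 25.5 completers analysed by ANCOVA are worth 25.5 / 0.75 = 34 per arm analysed by an unadjusted test.

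**Step 4: dependence on r and on the reading, at SD 3.75** (unadjusted power 80%).

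- If 3.75 is the SD of post-treatment scores, ANCOVA gives 83.5%, 89.9% and 97.5% at r = 0.3, 0.5 and 0.7. A change-score t-test would give 65.8%, 80.0% and 95.1%.
- If 3.75 is the SD of changes, ANCOVA gives 93.5%, 89.9% and 85.9%.

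The trend with r reverses between the readings, and only the r = 0.5 figure is common to both.

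**Step 5: simulation check.** With 4,000 runs, 25 per arm and a post-score SD of 3.75, the power at r = 0.3, 0.5 and 0.7 was 79%, 79% and 79% for post scores, 66%, 79% and 95% for changes, and 82%, 88% and 97% for ANCOVA. These agree with the formulas to within about two percentage points. All figures concern the t-test branch; the rank-sum branch was not simulated.

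**The case against.** The strongest reply is that nothing here is invalid. Allocation is randomised 1:1, so the unadjusted comparison is unbiased and keeps its type I error rate. That stands, and the point is one of efficiency only.

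Second, if changes are tested, as the Objectives and Sample size sections suggest, baseline is already used. This is partly right: it would be wrong to say that baseline is ignored. The use is still inefficient, by 8% to 19% of the SE over the range shown, and the analysis section should say which quantity is tested.

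Third, the size rests on assumed values. That also stands. Against post scores at r = 0.3 and SD 3.75, the gain is only 3.5 power points.

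A reader might go further and infer that the plan drops patients who miss a visit. The article does not say so. Its analysis section contains no missing-data rule, the Informed consent section keeps leavers' data for the final analysis, and such rules are commonly left to a full protocol or analysis plan that is not shown. Nor would a baseline-adjusted model cure that problem in general. The hormones have a single post-treatment sample, so ANCOVA loses the same patients as a t-test. A mixed model for the questionnaires adds only patients who have one of the two later visits.

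**Conclusion.** The point holds as a recommendation to gain precision. The article prescribes unadjusted two-group tests for six continuous outcomes that all have a baseline value, and it does not define the quantity tested. ANCOVA has the smaller standard error on either reading for any correlation between 0 and 1, under equal SDs at the two visits. With r = 0.5, the gain is 13% of the SE, or between 6 and 12 power points for PSQI over SDs from 3.25 to 4.5. The direction is firm. The size is not, because the article gives neither SD nor correlation. The documents do not support a charge of bias, of an inflated error rate, or of patients being excluded for missed visits.

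**What to change.** Replace the t-test/rank-sum rule for continuous outcomes with ANCOVA of the post-treatment value on arm and the baseline value of the same outcome. Report the adjusted difference between arms with its 95% CI.

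For PSQI, ISI and FSS this can be a mixed model over the 4- and 8-week visits with terms for arm, visit, arm-by-visit and baseline-by-visit. It includes every patient with at least one of those visits. For CRH, ACTH and CORT, use log values at both time points if the distributions are skewed.

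The cost is one degree of freedom for the baseline covariate in ANCOVA, a revised paragraph and a few lines of SPSS syntax (UNIANOVA or MIXED). No new data are needed. The change should be recorded before unblinding.

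### The between-group test is chosen from the outcome data by a rule that gives no test for normal data with unequal variances, and its rank-sum branch does not target the PSQI point difference used to size the trial

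*Protocol article*

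**What the plan says.** All statements are in the protocol article.

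- Statistical analysis, order of steps: for between-group comparisons of measured data, "first normal analysis will be performed". Neither the normality test nor its threshold is named.
- Statistical analysis, the rule: the t-"test will be used for the measured data conforming to normal and homogeneity of variance, and a non-parametric rank sum test will be used" where data are not normal. For the t-test both conditions must hold.
- Statistical analysis, second branch in full: "a non-parametric rank sum test will be used for non-normally distributed measured data".
- Statistical analysis, summaries: "The measured data will be expressed as mean ± standard deviation". This applies to all measured data, whichever test is used. No between-group difference or confidence interval is named for either branch.
- Sample size: "The calculation of sample size will be based on the change of PSQI scores". A systematic review is cited, by which "a clinically significant therapeutic effect is defined as a PSQI score gap of at least 2.7 points", and then "we estimate that there will be 3 points in each gap between the two groups after treatment".
- Outcome measures and Table 1: PSQI, ISI and FSS are taken at baseline and at two later visits (4 and 8 weeks). CRH, ACTH and cortisol are taken at baseline and once after treatment. PSQI and the three hormones are all primary.

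**The concern.** The rule has three weaknesses.

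1. It is incomplete. Equal variance is made a condition of the t-test, but nothing is said about what follows when data pass the normality check and fail that condition. The analyst would have to choose a test with the outcome data in view.
2. It lets chance choose the method. The same outcome at two visits, or three related hormones, can be compared by tests with different null hypotheses, for no reason other than how a pre-test fell.
3. It separates the analysis from the planning. The trial is sized on a difference in PSQI points. A rank-sum test compares whole distributions and gives no difference in points unless a shift estimate is added. The means and SDs shown beside it describe something else.

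At stake are a fixed target of estimation and a usable estimate for the primary outcomes. Control of false positives is not at stake.

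**Working it through.** **1. The plan's own figure, to fix the arm size.** The article states about 30 per group with 15% dropout, a 3-point difference and a significance level of 0.05. It gives no SD and no power, so 30 cannot be reproduced, only solved backwards.

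Formula: n = 2(z₀.₉₇₅ + z_power)² SD² / Δ², then N = n / (1 − 0.15). A two-sided test is assumed.

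- 80% power: n = 2(1.960 + 0.842)² SD² / 9 = 1.744 SD². N = 30 needs n = 25 (25 / 0.85 = 29.4, rounded up). That holds for SD 3.71 to 3.78 (1.744 × 3.71² = 24.0; 1.744 × 3.78² = 24.9).
- 90% power: n = 2.335 SD², so SD 3.21 to 3.27.

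The point does not depend on this. It only sets the range of interest: 30 per arm as randomised, and 30 × 0.85 = 25.5 after dropout.

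**2. The branches laid out.**

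| Normality | Equal variance | Test named |
|---|---|---|
| passes | passes | t-test |
| passes | fails | none |
| fails | passes | rank-sum |
| fails | fails | rank-sum |

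**3. How often each branch is entered when data are truly normal.** Assumed: Shapiro-Wilk in each arm, then mean-centred Levene, all at 0.05. There were 1,500 simulated data sets per cell. Shares are given for 30 / 26 per arm.

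| SD ratio | t-test | rank-sum | no test |
|---|---|---|---|
| 1 | 0.859 / 0.857 | 0.091 / 0.089 | 0.049 / 0.054 |
| 1.25 | 0.731 / 0.735 | 0.095 / 0.090 | 0.174 / 0.175 |
| 1.5 | 0.439 / 0.499 | 0.107 / 0.097 | 0.454 / 0.404 |
| 2 | 0.085 / 0.105 | 0.111 / 0.091 | 0.803 / 0.804 |

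Monte Carlo error is at most about 1.96 × √(0.45 × 0.55 / 1,500) = 0.025 near the middle of the range. Repeat runs over 25 to 30 per arm gave 4–5%, 15–18%, 39–46% and 77–83% in the no-test cell. A separate run of 6,000 trials at 25 per arm with SD 3 against 4.5 gave 35%; the form of Levene's test, which the plan does not fix, moves the figure by a few points.

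The first row can be checked by hand. Both arms pass normality with probability 0.95² = 0.9025. Rank-sum is then 1 − 0.9025 = 0.0975, and no test is 0.9025 × 0.05 = 0.045.

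**4. Mixed methods by chance.** Take 0.0975 as the chance that a truly normal outcome goes to rank-sum, and treat outcomes as independent (a simplification).

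- PSQI at two visits, exactly one by rank-sum: 2 × 0.0975 × 0.9025 = 0.18.
- Three hormones not all on the same side: 1 − 0.9025³ − 0.0975³ = 0.26.

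**5. Error rates.** With equal normal arms under the null, the rule rejects in 4.5% of trials. With SD 3 against 4.5 and the gap filled by the pooled t-test, it rejects in 5.4%, against 5.1% for Welch. Welch applied throughout gave 4.4% to 5.4% over SD ratios 1 to 2.

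**6. What a fixed estimate would give.** The 95% half-width for the mean PSQI difference at 26 per arm is t₀.₉₇₅,₅₀ × SD × √(2/26). For SD 3.5 this is 2.009 × 3.5 × 0.277 = 1.95 points. For SD 3, 4 and 4.5 it is 1.67, 2.23 and 2.51. An observed difference of 3 points with SD 3.5 would be reported as 1.05 to 4.95, which a reader can place beside 2.7 directly.

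**The case against.** Several objections are sound, and they limit the point.

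- **A reader might infer that 2.7 points is the trial's success criterion.** The text does not support this. The figure appears only under Sample size, as a clinically significant effect taken from a systematic review. It is not said to be a mean, and the only decision rule stated is the P value threshold. It is a reference for interpretation.
- **A reader might infer that the rank-sum branch leaves the trial unable to say how its result compares with 2.7 points.** That is too strong. Means and SDs are reported in both branches, so a crude difference, and from it an approximate interval, can be derived. What stands is that this difference does not correspond to the rank-sum test, and that no shift estimate is attached to that test.
- **No interval is named for the t-test branch either, and estimates are often left to an analysis plan that is not shown.** This is true, so a missing interval is not by itself a finding. The t-test does at least target the mean difference. The incomplete rule is a different matter, because the article states it.
- **A reader might infer inflated false positives or a large loss of power.** The error rates above show no material inflation. For PSQI-like integer scores with a true 3-point difference and SD ratio 1.5, power is 0.45 for the written rule against 0.66 for Welch. That counts every data set without a test as a non-rejection, whereas in practice an analyst would run some test, and with Welch in the gap the results are nearly identical.
- **The hormones may not be skewed.** The documents do not say. In one assumed lognormal scenario (log-SD 0.4), 72% of trials go to rank-sum and 28% do not, but this shows only that the split can be wide. It does not show that all three need a log scale.

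**Conclusion.** The concern holds in a limited form. The rule is data-driven and not exhaustive. With 25 to 30 per arm, the share of normal data sets left without a test is about 5% at SD ratio 1, 15–18% at 1.25 and 39–46% at 1.5. About 10% of truly normal data sets are sent to rank-sum by chance, so methods can differ across PSQI visits or hormones. The rank-sum branch does not target the point difference on which the trial is sized.

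The shares rest on assumed pre-tests at 0.05 and assumed SD ratios; the article gives none of these, so they are a range and not a forecast. The 5% and 10% figures follow almost directly from testing at 0.05. The missing branch itself needs no assumption.

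The gain from a change is a method fixed in advance and an estimate that can be interpreted. Type I error would hardly move.

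**What to change.** Drop the normality gate and name one method per outcome.

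- **PSQI, ISI and FSS:** report the between-group mean difference with 95% CI from a Welch t-test or a baseline-adjusted linear model, the same at both post-baseline visits. Interpret the PSQI result alongside the 2.7-point reference, without turning that reference into a success rule.
- **Hormones:** fix the scale (original or log) for each hormone before unblinding, and report the difference or ratio with 95% CI on that scale.
- **Rank-sum test:** keep it as a sensitivity analysis, with a Hodges-Lehmann shift and CI.

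The cost is a revised paragraph in the analysis section and minor analysis work. No visit, measurement or sample size changes.

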### Quality control

Training will be required for all participants, including acupuncturists, evaluators, and statisticians, to ensure the quality of the trials. The intervention will be based on strict adherence to standardized operating procedures. Both groups will be treated by acupuncturists with a medical master’s degree, licensed physicians, and clinical experience. All physician assistants will receive one-day professional training to familiarize them with treatment options.

To standardize clinical practices and provide clinical quality assurance, a set of clinical management practices will be developed to ensure consistency among different participants. This is helpful for management of archives, standardizing operations, as well as ensuring the feasibility and safety of the clinical research.

## Discussion

Acupuncture for the treatment of mental illness, especially insomnia, has the advantages of being low-cost, having clinical efficacy, having few side effects, and being able to be carried out in agreement with a variety of treatments. However, the mechanism of acupuncture in treating insomnia remains elusive. Therefore, we designed this single-center, single-blind, randomized, placebo-controlled clinical trial to initially validate our hypothesis. In this study, the sham acupuncture group will be used as a control group to compare the effect of acupuncture. At present, clinical research on acupuncture uses various types of sham acupuncture methods, including acupuncture on non-TCM acupoints, sham lasers on acupoints, and placebo needles [38]. In order to maximize the blinding effect of participants, this study will use a placebo needle (similar to Streitberger’s design [39]), which has a similar appearance to the needle used in the acupuncture group but has a blunt tip that does not penetrate into the skin, and both groups of participants will wear eyeshades during treatment to maximize participants’ blindness.

However, there are still some limitations in this study. 1) Two blood tests will be required before and after treatment, which will impose some difficulties on recruitment. 2) The majority of Chinese patients have some understanding of acupuncture treatment; thus, the non-invasive placebo acupuncture method in the sham acupuncture group may make the participants suspicious and interfere with treatment. For this purpose, we will require participants to wear eyeshades and train acupuncturists to answer participants’ questions during the treatment. 3) The single-center experimental design will result in a single sample, with limited representativeness, and possible experimental bias. More influencing factors should be considered and the result should be further verified and explored in a large sample population.

